### Procedure

Subjects attend an initial session with their respective trainer for 90 to 120 minutes, including orientation to the computer tablet. Subjects are provided with a prepared study tablet and printed reference handbook to engage in their home training program for 2 weeks, with a minimum of 150 minutes of tablet-based activity per week. After 2 weeks, subjects attend a second session with their trainer for 60 to 90 minutes and then continue with their home training program for an additional 2 weeks. The trainer makes follow-up telephone contact at the end of weeks 1 and 3.

### Extra wheeling

The EPIC Wheels program requires trainees to engage in wheelchair activity that they might not otherwise undertake. While it is unlikely that such additional wheelchair use alone would substantially increase skill acquisition or proficiency, to address this potentially confounding variable subjects are randomly allocated into extra wheeling and non-extra wheeling subgroups. Subjects in the extra wheeling subgroups are asked to perform an additional 75 minutes of unstructured wheelchair wheeling per week, which can occur in their home or in the community. Extra wheeling is defined as participants propelling their wheelchair in addition to what they would typically do in the course of daily activities. For these subjects, the training tablet presents a prompting question every 24 hours asking how many minutes of extra wheeling they have performed. Subjects toggle up and down in 5-minute increments and enter their data before the tablet returns to the training activities. Trainers can encourage subjects to increase their extra wheeling activity during follow-up phone calls and training visits if target levels have not been met.

### Intervention

#### Treatment group (EPIC wheels)

EPIC Wheels trainers are occupational therapists with ≥5 years of clinical experience in wheelchair provision and training, who have received a 2-day comprehensive orientation program. Each training session is administered using a protocol and checklist. Trainers select a subset of skills and training activities to incorporate into the home training program based on ability, safety, and relevance for the subject. The EPIC Wheels home program includes a comprehensive, structured library of educational material and training activities, organized in a hierarchy from simple to complex. Trainers monitor a subject’s progress through online access to tablet usage data and re-assessment during the second training session, revising the home program with more advanced skills and activities.

The home program component is delivered using a 10-inch (≈25 cm) portable ASUS® computer tablet (ASUSTek, Markham, ON). The tablet is menu driven and interactive, using a touch-screen interface. Training is provided in a multi-modal format with illustrations and videos, allowing detailed step-by-step guidance and slow-motion demonstrations. Female and male actors, both close to 70 years of age, were used to provide age-appropriate models in the videos. Practice activities can be clearly demonstrated and include imitative, function-based, and interactive game-related activities. The tablet is mounted on a rigid platform with a simple strap that wraps around the subject’s thighs for use in a wheelchair. A 'progress’ icon provides daily updates on the number of minutes practiced per week to reinforce adherence. Subjects can exchange voicemail with their trainer using an integrated applet. Subjects receive a mobile Internet device for voicemail and data transfer or update capability, but the tablet operates as a single-function device with all other applications disabled.

#### Control group (cognitive training)

Control group subjects also attend two sessions with their trainer to address attention balance through exposure to study personnel. In addition, they receive an identical tablet pre-loaded with computer games to account for tablet device and activity exposure. Nine different games address problem solving (for example, Tetris, Cogs); word, math, and memory challenges (for example, Scrabble, Sudoku); and dexterity or response skills (for example, Marble Saga, Cut the Rope). Each training session is administered using a protocol and checklist. During the first session, the trainer discusses the potential benefits of computer-game training on cognition and motor function, and how these can positively impact wheelchair mobility. Trainers provide an orientation to the cognitive games and operation of the tablet device. During the second session, the trainer discusses subjects’ current community activities and experience using the wheelchair via a structured discussion guide, and provide verbal information related to barriers encountered, as well as any additional review or training related to the cognitive training games. To minimize attrition and provide wheelchair skill-specific information, the consent form informs control group subjects that they will receive a DVD with a condensed EPIC Wheels education program after the post-intervention data collection is complete.

### Training schedule

The home training schedule for both groups targets a minimum of 1 or 2 sessions/day, 15 to 30 minutes in length, at least 5 days per week (minimum 150 minutes/week). These guidelines are based on the National Blueprint consensus document on promoting physical activity for adults over 50 years, which advocates that lifestyle- or endurance-related activity of moderate intensity should be undertaken for at least 30 minutes (in bouts of at least 10 minutes) 5 to 7 days per week [39]. The minimum training time is at least comparable to 1:1 training time in other clinical studies using structured wheelchair skills training, where a significant improvement in skill capacity was observed [17-19]. Adherence to this schedule is achievable, as demonstrated by a study of home-based training program for improving hand function among stroke survivors (*n* = 77; *m* = 57 years) which obtained 96% compliance for 1.3 hours of training per day, 7 days per week over 5 weeks [40].

### Safety

The EPIC Wheels program incorporates extensive safety-related material, including teaching the safest mobility strategies; use of safety equipment; recognizing unsafe situations; and seeking assistance when skills are insufficient to address environmental barriers. At the initial training session, subjects are provided with protective wheeling gloves. Caregivers attend and participate in both training sessions and encouraged to supervise home training activities. A fitted spotter’s strap and demonstration and instruction are provided for caregiver use during training to prevent wheelchair tips. Operating a wheelchair in the community carries innate risks that cannot be entirely eliminated; however, EPIC Wheels offers education and training designed to minimize risks of wheelchair operation. This knowledge should reduce the risk of a fall or injury that subjects might be exposed to in their everyday use of a MWC had they not received this program. Any unsafe performance observed during training is addressed immediately with corrective feedback. Subjects are encouraged to contact the coordinator immediately if they experience unusual discomfort, pain, or physical symptoms. A data and safety monitoring board, consisting of a statistician, a physiatrist, and a physical therapist, review accumulating indicator data and advise the investigators regarding safety issues, evidence of benefit, and need for modification to the study design [41]. Adverse events are documented by the trainer and reported to the data and safety monitoring board and the ethics review board.

### Computer technology uptake

The use of a computer tablet to deliver the home training program offers advantages of portability, audiovisual versatility, flexible configuration, and real-time updating. Although older adults are less likely than younger people to embrace technologies, such as computers, their use of computers continues to grow. Studies in the United States between 2006 and 2010 found 84% of those over 60 years had experience with computers [42] and 40% of those over 65 years are regular computer and Internet users [43]. Use of a tablet involves some new learning, and age-related declines in memory and fluid intelligence may restrict uptake. These issues are addressed through self-paced training, structures for successful experiences to build confidence, and by adapting the interface for familiarity and ease of use with minimal memory requirements [44,45]. Consumer, caregiver, and clinician input were incorporated during the EPIC Wheels program development to ensure the delivery format addresses these concerns.

### Data collection

At baseline, wheelchair device characteristics are collected using a modified wheelchair specification form [46]. Descriptive characteristics including age, sex, marital status, highest level of education, primary diagnosis related to MWC use, length of time using the MWC, and propulsion method are collected along with cognitive status measured using the Standardized Mini-Mental Status Exam [47]. Handgrip strength has been demonstrated to be an accurate surrogate measure of overall strength [48] and is measured using a Jamar^TM^ 5030J1 dynamometer (Sammons Preston Rolyan, Chicago, IL).

Feasibility indicators for process, resources, management, and treatment characteristics are collected during study administration and at the study’s end. Process indicators include recruitment, consent, and retention rates at each site. Retention is a critical factor for subsequent clinical trials; follow-up with all discontinued participants regarding their reason for dropout will inform future study design and sample size calculations. A post-treatment participant questionnaire is used to evaluate perceived benefit. Resource indicators are monitored by tracking study staff time logs and tablet usage data. Management issues are evaluated using a trainer evaluation form and by tablet reliability or loss data. Treatment indicators include reporting of adverse events and statistical analysis of the treatment effect.

The clinical outcome measures are collected at baseline (pre-randomization) and post-treatment (1 month). The primary outcome is wheelchair skill capacity, measured using the Wheelchair Skills Test 4.1 (WST) [14]. The WST is a structured assessment with 32 discrete mobility skills required to perform social roles in the community, each scored dichotomously as pass or fail, producing a total skill capacity score (0 to 100%) with a higher score reflecting more skills acquired. The WST is sufficiently sensitive to detect proximal effects of training; can be completed in approximately 30 minutes; and does not demonstrate floor or ceiling effects [16]. Two systematic reviews of available wheelchair skill outcome measures confirmed that the WST has the strongest psychometric properties and has been used most extensively in clinical trials [49,50]. The WST has demonstrated reliability for test-retest (intraclass correlation coefficient (ICC) = 0.90), intra-rater (ICC = 0.96), and inter-rater (ICC = 0.97) administration [16]. Construct validity has been supported by significant relationships with predictive variables of age, sex, MWC experience, diagnosis, and use of a lightweight wheelchair, which together accounted for 35% of variability in WST score using multiple regression (adjusted *R*^2^ = 0.35) [16]. Concurrent validity has been established through positive correlation with two criterion measures: therapists’ global assessment of user ability (*R*_S_ = 0.39 - 0.40) and the Functional Independence Measure (admission score *R*_S_ = 0.38; discharge score *R*_S_ = 0.31) [16,51].

Secondary clinical outcomes reflect more distal impacts of the intervention. Given the dearth of evidence in the literature, there is substantial value in understanding the relationship between skill acquisition and safety, confidence, community participation, mobility, and utility. Seven secondary measures contribute to discerning a clinically important impact of the EPIC Wheels intervention.

• WST 4.1 skill safety. The WST also provides a total skill safety score (0-100%) reflecting the number of skills addressed in a safe manner (higher score indicates greater safety), regardless of whether the skill is acquired or not. This is of considerable importance, since training also involves learning to recognize risks and limitations.

• Wheelchair Outcome Measure (WhOM). The rehabilitation literature strongly suggests the use of measures of user-identified activities of relevance and perceived satisfaction with performance [52-54]. Using an interview format, MWC users are asked to identify relevant activities and rate them for both importance and satisfaction, using an 11-point scale (0 to 10), with higher scores indicating greater importance or satisfaction. The WhOM demonstrates reliability and validity in use among older adults (Test-retest ICC = 0.77 to 1.00; correlation with QUEST [55]*r*_
*s*
_ = 0.36 to 0.45) [56].

• Wheelchair Use Confidence Scale for Manual Wheelchair Users (WheelCon-M 3.0). Self-efficacy has been identified as a key component in the performance of wheelchair mobility skills [57] and preliminary research has suggested that standardized training can increase wheelchair confidence among older adults [58]. The WheelCon is a self-report questionnaire composed of 65 statements related to confidence using a wheelchair in activities and environments, each rated on a scale from 0 (not confident) to 100 (completely confident), producing a total mean score of 0 to 100 [59]. A 2010 study evaluated test-retest reliability (ICC = 0.84) and significant correlation with comparison measures supporting its validity [60].

• Life-Space Assessment (LSA). The LSA is a 20-item questionnaire that tracks the wheelchair user’s travel on a continuum of five environments from the home to outside of town [61], and capturing mobility habits over a 4-week period, including frequency of travel and level of assistance required. Scores vary from 0 to 120 and are weighted for frequency and level of assistance, with higher scores reflecting further distance from home, greater frequency of travel, and less assistance required. Evaluation of the LSA among power wheelchair users found excellent test-retest reliability (ICC = 0.87) [62].

• Health Utility Index Mark 3 (HUI3). Health utility measurement is useful in performing cost-utility and cost-effectiveness analyses of new rehabilitation interventions. National guidelines for healthcare economic analyses strongly advocate the use of a validated measure of health-related quality of life, which can be converted to quality-adjusted life years gained, so as to fully inform funding decisions [63]. The HUI3 is a brief questionnaire that asks subjects about their health status, deriving both single- and multiple-attribute utilities to ascertain quality-adjusted life years [64], and meets the criteria for a valid health-related quality-of-life utility score [65]*.* Each single-attribute utility is scored between 0.00 and 1.00 and the multiple-attribute utility scale is scored from -0.36 to 1.00, with higher scores reflected better health and quality of life. Our study is not sufficiently powered to undertake a cost-utility analysis, but will determine the feasibility of collecting cost-utility data in a larger RCT and estimate what changes in health-related quality of life might be anticipated.

• Wheeling While Talking test (WheelTalk). Wheelchair mobility is a complex skill and prone to risk of tips, falls, and potential injury, particularly with older adult users, where motor and cognitive function may decline with age. The WheelTalk is a new divided-attention assessment for wheelchair users. Scoring reflects the additional number of seconds required to complete a slalom course during the dual-task versus motor task-only condition, with a larger time differential indicating poorer performance. Initial evaluation with residents in a long-term care facility demonstrated reliability for test-retest (ICC = 0.92), intra-rater (ICC = 1.00) and inter-rater (ICC = 1.00) administration [66]. Collecting data in this study will allow investigation of associations between performance and wheelchair skill, safety, and other demographic factors, contributing to validation of this tool.

• Data logger. To capture level of activity while in the wheelchair, a data logger (three-axis self-recording accelerometer X16-1C, Gulf Coast Data Concepts, Waveland, MS) is mounted on the drive wheel spokes of each subject’s wheelchair. The data logger is a small, unobtrusive 'black box’ that collects drive wheel movement via an accelerometer over a period of 6 to 10 days. Distance travelled and bouts of travel will be calculated, with larger values reflecting more activity. Collecting these data will allow description and comparison of wheeling patterns and extent of activity among participants. Data loggers are installed at the first training session and removed at the second training session, approximately 2 weeks later.

### Statistical analyses

Study analyses will consider study feasibility indicators as well as clinical (statistical) outcomes. Means and standard deviations (for continuous variables) and frequencies and proportions (for categorical variables) will be used to summarize case mix and outcome variables for groups. Qualitative comparison of variable balance will be made, including determination of prognostic importance [36]. Descriptive statistics of training time and number of training sessions (collected via tablet usage data) will be used to evaluate adherence and explore potential associations between training intensity and measured outcomes.

A detailed description of the feasibility indicators and measurement criteria is provided in Additional file 1. Feasibility indicators will be treated as binary, with 'success’ indicating that the protocol is sufficiently robust to move forwards with the large RCT with only small or no adaptation required, and 'revise’ indicating a need for more substantive change before proceeding. The number and extent of objectives requiring revision will determine whether the feasibility study data can be conflated with those produced in a larger subsequent RCT.

Post-treatment WST skill capacity scores will be compared in the treatment and control groups using analysis of covariance (ANCOVA), controlling for baseline score as a covariate for the primary analysis [67]. Borm *et al*. [68] demonstrate that correlation between pre- and post-intervention scores (*ρ*) influences analysis power; when *ρ* > 0.5, change score is more powerful than direct post-intervention comparison. However, when *ρ* lies between 0.2 and 0.8, ANCOVA (controlling for baseline score) further reduces the required sample size by 10 to 40% over change score. Given that preliminary data suggest *ρ* ~ 0.5 ([name], personal communication), ANCOVA should provide the most powerful analysis, in addition to reducing error variance and allowing modification when statistical assumptions are not met [69]. Unequal cell sizes will be accommodated using Method 1 adjustment [70] and diagnostic assessments made for model assumptions. Significance testing (*P*) and marginal means with 95% confidence intervals will be estimated. Effect size (partial *η*^2^) will be calculated as a ratio of the effect and total sums of squares, with a 95% confidence interval. To preserve prognostic balance, primary analysis will be based on intention to treat; however, since one objective is to estimate the treatment effect, secondary analysis on a per-protocol basis (subjects who adhere to treatment) will also be conducted, for comparison [71].

One argument for potential improvement in wheelchair skills using the EPIC Wheels program is the inducement of subjects to use their wheelchair more, rather than the specific content of the training program. Our factorial design, with extra wheeling as a second factor, will attempt to address this question. Initial analysis will contrast the two main effects: training (EPIC Wheels versus cognitive games) and extra wheeling (yes versus no). Secondary analysis of the interaction contrast between factors may delineate whether additional wheeling has a synergistic or antagonistic effect on the training program.

ANCOVA will be used to compare post-treatment scores between groups for WST skill safety, wheelchair confidence (WheelCon), safety risk (WheelTalk), and mobility (LSA) as a secondary analysis. In each case, baseline score will be used as a covariate. Subjects’ satisfaction with performance of meaningful activities (WhOM score) will be analyzed using analysis of variance (ANOVA). Mean administration time for the HUI3 will be calculated and a preliminary evaluation of change in the treatment group will be conducted. Endpoints and change analyses will also be conducted to compare their precisions with ANCOVA. Summary and descriptive statistics for distance and speed (mean and standard deviation) and bouts of activity (counts) will be calculated for the data logger data.

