**Discussion:**

The EPIC Wheels training program offers several innovative features. The convenient, portable, economical, and adaptable tablet-based, home program model for wheelchair skills training has great potential for clinical uptake and opportunity for future enhancements. Theory-driven design can foster learning and adherence for older adults. Establishing the feasibility of the study protocol and estimating effect size for the primary clinical outcome measure will be used to develop a multi-site randomized controlled trial to test the guiding hypotheses.

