#### Primary clinical outcome

The aim of the study is to evaluate the effect of EPIC Wheels on wheelchair skill capacity and obtain an estimate of the treatment effect size.

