### Sample size

To address the feasibility indicators, the number of subjects is large enough to represent the target population and assess the feasibility criteria [36]. In addition, the sample size is powered to detect a statistically significant difference between groups and provide a reasonable estimate of a treatment effect. With a 2 × 2 factorial design, sample size can be calculating using each main factor independently, and then determined by selecting the larger of the two estimates [37]. Our calculations are based on the primary clinical outcome measure (the Wheelchair Skills Test version 4.1, WST), as this will be used in subsequent EPIC Wheels studies. Research in the field of wheelchair skills training is still maturing, with three published studies using actual users, and given the novel home program approach an α of 0.10 was selected to ensure a potentially beneficial treatment effect would not go undetected (Type I error rate). Given the absence of data regarding the impact of extra wheeling, we opted to use a comparable effect size (*f* = 0.54) in the second factor calculation. To minimize the risk of identifying such an effect merely by chance (Type II error), the study is powered at 90%. Based on a sample size calculation for analysis of covariance (ANCOVA) each of the four groups would require eight subjects for a total of 32 participants. In previous Canadian trials, a 9 to 18% dropout rate has been reported; conservatively adjusting for a 25% dropout rate (32/0.75), a total study *N* of 44 is planned (*n* = 11 for each group).

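### The effect size is called partial η² but defined as effect over total sum of squares, which is classical η² and smaller in this ANCOVA

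*Protocol article*

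**What the plan says.** The primary analysis in Statistical analyses is an ANCOVA of post-treatment WST capacity, "controlling for baseline score as a covariate for the primary analysis". Training and extra wheeling are the two main effects, and their interaction is a secondary analysis. The section gives partial η² as the effect size and states that it "will be calculated as a ratio of the effect and total sums of squares, with a 95% confidence interval". It also reports that "preliminary data suggest *ρ* ~ 0.5".

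The effect size is a declared product of the study. Under Primary clinical outcome the aim includes to "obtain an estimate of the treatment effect size", and the Discussion paragraph of the abstract says that "estimating effect size for the primary clinical outcome measure will be used to develop a multi-site randomized controlled trial". The planning value in Sample size is Cohen's f: for extra wheeling, "we opted to use a comparable effect size (*f* = 0.54) in the second factor calculation".

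**The concern.** The name and the formula denote different quantities, and nothing else in the article says which is meant.

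- Classical η² = SS_effect / SS_total.
- Partial η² = SS_effect / (SS_effect + SS_error).

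They agree only when no other term in the model explains any variation. Here the total also contains the baseline covariate, the second factor and, where fitted, the interaction.

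Two things are at stake. A reader who trusts the label would take the figure as partial η², convert it by f² = η²p / (1 − η²p), and get too small an f for the later trial. The written ratio also shifts with the baseline correlation and the extra-wheeling effect, so it does not transfer to a trial that differs in either respect. The promised confidence interval has no clear target until label and formula agree.

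**Working it through.** **Inputs.** f = 0.54, 90% power, four equal groups and 32 participants before dropout (Sample size); "an α of 0.10 was selected" (same section); ρ about 0.5, with 0.2 to 0.8 as the range the plan discusses for ANCOVA (Statistical analyses).

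**1. Reproduce the plan's figure.** Use the noncentral F distribution with noncentrality N·f², 1 numerator degree of freedom and N − 5 denominator degrees of freedom (four groups, one covariate). With f = 0.54 and alpha 0.10, 90% power is first reached at N = 31. Rounding to equal groups gives 32 (power 0.909), as the plan states. The plan's f therefore behaves as an effect relative to error variance, which is the scale that partial η² converts to.

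**2. Express both ratios.** Set SS_error = 1, with balanced cells, no interaction and f on the covariate-adjusted scale.

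- Effect: f² = 0.54² = 0.2916
- Covariate at ρ = 0.5: ρ² / (1 − ρ²) = 0.25 / 0.75 = 0.3333
- Extra wheeling: 0, or 0.2916 if it also has f = 0.54

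**3. Compute at ρ = 0.5.** Implied f is √(ratio / (1 − ratio)).

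| Quantity | Calculation | Value | Implied f | N (alpha 0.10, 90% power) |
|---|---|---|---|---|
| Partial η² | 0.2916 / 1.2916 | 0.226 | 0.54 | 31 |
| As written, extra wheeling null | 0.2916 / (0.2916 + 1 + 0.3333) | 0.179 | 0.468 | 41 |
| As written, extra wheeling f = 0.54 | 0.2916 / (0.2916 + 1 + 0.3333 + 0.2916) | 0.152 | 0.424 | 50 |

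In the main case 41 / 31 = 1.32.

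**4. Vary ρ, extra wheeling null.** At ρ = 0.2 the covariate term is 0.04 / 0.96 = 0.0417, the ratio is 0.219 and N is 33. At ρ = 0.8 the term is 0.64 / 0.36 = 1.778, the ratio is 0.095 and N is 84.

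**5. Direction.** SS_effect + SS_error cannot exceed the corrected total, so the written ratio can never exceed partial η². In 3,000 simulated trials (N = 32, ρ = 0.5, extra wheeling null) it was smaller in every one.

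**6. Behaviour in samples of this size.** Those simulations gave mean sample values of 0.259 for partial η² and 0.193 for the written ratio, against a true partial η² of 0.226. A repeat with 10,000 trials gave 0.260 and 0.194. Converted to f, these are 0.59 and 0.49, which imply N = 27 and 38 against 31. Correcting the formula alone therefore does not give an unbiased planning value.

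**The case against.** The strongest reply is that the measure is correctly named and only a descriptive clause is loose. An analyst who reports what the plan names, using standard software output, would report true partial η², and only the wording would be wrong. The hypothesis test, P value and marginal means do not use this clause. That stands and limits the severity.

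A reader might infer that the next trial will be sized wrongly. The article does not support that. It says an effect size will inform the later trial, but not that partial η² will be the input. It bases this trial's own planning on a WST mean change and SD (9.3% and 9.5%), and it already promises marginal means with intervals. The harm needs the literal ratio to be computed, read as partial η² and converted to f.

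A reader might also infer that the point estimate and its interval will be on different scales. That assumes a noncentral-F interval, and the article names no interval method.

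The total of 50, about 60% too many, needs extra wheeling to have f = 0.54. The plan adopted that value for want of data, and the Extra wheeling section considers a substantial effect of added wheeling alone unlikely. About 30% is the fairer main case.

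Finally, at this sample size the two statistics miss the true partial η² by similar amounts in opposite directions, and sampling error is larger than either miss: the simulated 95% range for sample partial η² at N = 32 was about 0.04 to 0.52. This does not excuse the mislabel, but it rules out presenting the corrected formula as a complete remedy for planning.

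**Conclusion.** The definition is wrong as written: the formula is classical η² under the name partial η². In this model the written ratio is systematically smaller. The direction is certain; the size depends on ρ and on the extra-wheeling effect. At f = 0.54 and ρ = 0.5 it is about 0.18 instead of 0.23, provided extra wheeling has no effect.

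The consequence for planning is conditional. If the figure is converted to f, the later trial would be about 30% too large (41 against 31), assuming the same design, alpha 0.10 and 90% power. Alpha 0.10 was justified only for the present study, so those totals illustrate the scale and do not forecast the next trial. The error is towards a larger trial, not an underpowered one.

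Classical η² is a legitimate measure in itself; the fault is the mismatch. Severity is minor to moderate, because this trial's inference is untouched.

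**What to change.** In Statistical analyses, define partial η² as SS_effect / (SS_effect + SS_error), and state that the 95% confidence interval is constructed for that same quantity.

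Add that the adjusted mean WST difference with its confidence interval and the residual SD will be reported as the planning inputs for the multi-site trial, or that a bias-corrected effect size will be used. Planning should not rest on the point estimate of partial η² alone.

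The cost is one corrected clause and one added sentence. The quantities come from the ANCOVA already planned, and design, data collection and primary test do not change. The one caution is the upward bias of sample partial η² at about 32 participants, which the added sentence addresses.
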